#### Necrotizing Enterocolitis

Necrotizing enterocolitis may be diagnosed at surgery, at postmortem or clinically and radiologically: at least one of the following clinical signs present: bilious gastric aspirate or emesis, abdominal distension, or occult or gross blood in stool AND at least one of the following radiological features: pneumatosis intestinalis, hepatobiliary gas, or pneumoperitoneum. Infants who satisfy the definition of NEC but at surgery or postmortem have a “focal gastrointestinal perforation” will not be coded as having NEC.

All diseased cases meeting the predefined case definition of NEC or LOS will have samples analyzed (expected total ~70–100 infants). Samples from up to 200 non-diseased cases will be selected to ensure sufficient coverage of intervention arms using matching algorithms and coverage of other clinical risk factors and outcomes. We will also analyze samples from non-diseased cases to determine microbiomic and metabolomic profiles between trials arms.

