### Sample Size Estimates

Sample size requirements for each element of this study have been evaluated and are based on both published data and practical/logistical aspects from our existing work and that from other published studies. These considerations include
The duration, estimated start time, and recruitment rate for ELFIN, along with the estimated start date for MAGPIE and logistical issues in establishing recruitment from 10 hospital sites.The trial efficacy and disease event rate will not be known until the main trial completes. The incidence of NEC (Bell stage 2 or greater) is expected to be 5–10% and for LOS <20%, and some infants will have both diseases. Recruiting 480 infants will identify between 70 and 100 “disease” cases, 10–20 cases requiring gut surgery, and provide well sampled “non-diseased” infants with varying clinical risk factors, exposures, and outcomes.VOC analysis may identify several individual compounds; in our recent paper publishing the methodology, we show that on average 31.3 ± 10.5 (mean and SD) VOCs were identified per sample (82). At a power of 80%, and two-sided significance at the 5% level, we would need 50 infants per trial intervention group to show an increase in 5 VOCs. The SD for each sample was 2.9 ± 1.3 compounds and on average 90% of the VOC abundances showed a coefficient of variation smaller than 30%. Our data also showed in a study of 13 infants, which VOC number in healthy neonates significantly increased with age (0.49 extra VOCs per day 95% CI 0.12–0.86), a trend not seen in those who developed NEC (64).Microbiomic data complexities means that the sample size necessary to evaluate the actions of different interventions and the incidence of disease is dependent on effect size, the number of interacting factors, and their correlation. For a power of 80% to detect a 50% difference in community profile patterns arising from a categorical descriptor of microbial community variation, using a two-sided test at a significance level of 5%, the study needs ~200 samples. In our previous studies (1) 12 twin pairs analyzed (gut microbial profiling) using PLS-DA showed highly significant correlations between pairs (53) and (2) examination of 136 samples from 32 patients (*n* = 20 NEC or LOS) showed significant differences (*p* = 0.002) in microbiomic patterns between diseased and healthy individuals (24).Using immunohistochemical data from our group (83), and assuming that any differences between disease and control will be greater than those in healthy individuals, and using a two-sample *t*-test, our proposed sample size of 20 would give 80% power to detect a difference of 0.66 (66%) in cells/crypt cross section at a significance level of 5% and an approximated SD of 0.5 (50%).Mixed-effects models, which we propose for modeling the direct effects of the microbiome on disease risk, are economical with power because the residual variance of these models is smaller since some of it is accounted for in the random effect. Using the method by Cohen (84), we calculate that a GLM would have a power of 82% with 10 predictors and 50 for a “large” effect size (*f*^2^ = 0.35, *R*^2^ = 0.51) at the 5% level of significance, and a power of 47% for a “medium” effect size (*f*^2^ = 0.15, *R*^2^ = 0.36) at the 5% level of significance. With *n* = 100 the calculated powers are 99% for a large effect size and 74% for a medium effect size. Including random effects in the GLM would increase power at the same effect size or conversely permit smaller effect sizes at the same power. The power analysis of an SEM is altogether more complex because it relies on the goodness-of-fit criteria selected for the model. Power at the model level may be low when there are few model degrees of freedom even for a reasonably large sample size; requiring greater than 100 samples if there are fewer than 20 model degrees of freedom (85). We will supplement these models where needed using a Bayesian SEM approach.

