
### Statistical Analysis

There are three major modeling issues that have to be addressed in this analytical pathway:
(i)the multivariate nature of the microbiome and metabolome, and data generated from immunohistochemistry;(ii)the longitudinal/developmental component in the neonate, which will lead to repeated measures of disease state and microbiome on the same individuals, and(iii)the interdependence and interactions between different predictors, which may have both direct and indirect effects on incidence and progression of disease.

The analytical approach used in this study will focus on modeling the relationship between putative risk factors, trial interventions, and incidence of NEC and LOS from longitudinal data capturing variation in both risk factors and disease through time, and the any differences in non-diseased cases between trial arms. We will use a progressive modeling strategy based on combining multivariate analyses of micro- and metabolomic immunological data, with mixed-effect modeling of outcome in relation to drivers of disease; and finally, mixed-effect SEM to quantify the importance of interacting factors and drivers. Specifically, we will
(i)quantify the impacts of individual risk factors in causing disease;(ii)quantify the effects of direct and indirect risk factors on disease;(iii)quantify the dynamics of pathogens, the neonatal microbiome, the immune response, and their impact on outcomes, and(iv)identify the impacts of trial interventions and clinical management on the drivers and disease.

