### Quantifying the Direct and Indirect Impact of Risk Factors on Disease

We will use repeated measure mixed-effect modeling to quantify the direct effects of microbiome on risk of disease while adjusting for clinical factors. We will use case as the random effect and adjust for autocorrelation in the response using appropriate correlation structures in the model. The applicants have used this approach extensively to investigate the epidemiology of food-borne pathogens (92). We will use an SEM approach to quantify direct and indirect effects of risk factors on the incidence of disease. We will develop a set of models that characterize the relationship between clinical factors, the changes in gut microbial community types, developmental stage (postnatal and postmenstrual age), and comorbidities associated with disease onset and then challenge the model with the data derived from the laboratory and clinical data collection (93).

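### The 82%, 47%, 99% and 74% printed for the disease-risk mixed models are not powers of that analysis: three do not follow from the formula cited, and all four describe another test at other sample sizes

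*Protocol article*

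**What the plan says.** The last item under Sample Size Estimates begins "Mixed-effects models, which we propose for modeling the direct effects of the microbiome on disease risk", and so ties what follows to the disease model. It then turns to Cohen's method: "we calculate that a GLM would have a power of 82% with 10 predictors and 50 for a “large” effect size". The four figures, all for 10 predictors and a 5% test, are:

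- n = 50, large effect (f² = 0.35, R² printed as 0.51): 82%
- n = 50, medium effect (f² = 0.15, R² printed as 0.36): 47%
- n = 100: 99% (large) and 74% (medium)

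It adds that random effects would raise these powers.

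The section Quantifying the Direct and Indirect Impact of Risk Factors on Disease describes the model itself: "We will use repeated measure mixed-effect modeling to quantify the direct effects of microbiome on risk of disease while adjusting for clinical factors". The Statistical Analysis section gives the response as disease incidence: "modeling the relationship between putative risk factors, trial interventions, and incidence of NEC and LOS from longitudinal data". The case definitions make NEC and LOS present or absent, confirmed by blinded review. On numbers, the Necrotizing Enterocolitis subsection expects about 70–100 diseased infants, all analysed, and says "Samples from up to 200 non-diseased cases will be selected".

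**The concern.** The calculation and the analysis do not describe the same thing. Cohen's f² with ten predictors is a joint F test in a linear model. No number of cases, odds ratio or within-infant correlation enters it. The planned model asks what the microbiome adds after clinical adjustment, for a case/non-case response with repeated records, in 270–300 infants.

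These are the numeric powers the protocol attaches to the disease-risk model. A reader who relies on them would believe that 50 observations give 82% power with ten predictors. That is not so even for the test the formula does describe.

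**Working it through.** **1. Reproducing the printed figures.** The inputs, all from Sample Size Estimates, are u = 10 predictors, n = 50 or 100, f² = 0.35 or 0.15, and α = 5%. Cohen's test has v = n − u − 1 denominator degrees of freedom (39 or 89) and noncentrality λ = f²·n. Power is the probability that a noncentral F(u, v, λ) exceeds the 95th percentile of the central F.

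| n | f² | λ | Printed | Formula |
|---|---|---|---|---|
| 50 | 0.35 | 17.5 | 82% | 72.6% |
| 50 | 0.15 | 7.5 | 47% | 32.6% |
| 100 | 0.35 | 35 | 99% | 98.8% |
| 100 | 0.15 | 15 | 74% | 70.7% |

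Three do not reproduce. Variants do not rescue them (same order as the table):

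- chi-square test on 10 df: 83.5%, 40.7%, 99.4%, 76.0%
- α = 10%: 83.3%, 46.2%, 99.5%, 81.2%
- testing only 7 of the 10 predictors: 81.1%, 39.8%, 99.5%, 78.4%

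A grid over α, the number of tested terms, and offsets in v and λ still misses at least one figure by 3.6 points.

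A separate slip sits in the same sentence. R² = f²/(1 + f²) gives 0.35/1.35 = 0.26 and 0.15/1.15 = 0.13. The printed 0.51 and 0.36 are the square roots, that is, R.

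**2. Does the yes/no outcome matter?** It depends on the scale of f².

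- *f² as variance explained in case status.* The F test is then the two-group discriminant test, with f² = p(1 − p)D², where p is the case fraction and D the standardised distance between groups. Simulating fixed case and non-case groups with normal predictors at 20–50% cases gives 71–74%, 31–33%, 99% and 70–71%. These are the formula's values, so nothing is lost.
- *f² on an underlying liability (an assumption; the protocol mentions no such scale).* With ten normal predictors, liability R² = f²/(1 + f²), one record per infant and 20–50% cases, the F test has about 30–42% (large) and 14–19% (medium) at n = 50. At n = 100 it has about 67–84% and 33–44%. Repeat runs move the ends of these ranges by about two points.

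**3. The planned numbers.** For one microbiome covariate in a logistic model with one record per infant, an approximate detectable log odds ratio per SD at 80% power and two-sided 5% is b = 2.80/√[N·p(1 − p)(1 − ρ²)]. Here ρ² is the share of the covariate's variance explained by the other predictors.

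| Cases / total | N·p(1 − p) | OR, ρ² = 0 | OR, ρ² = 0.5 |
|---|---|---|---|
| 70/270 | 70 × 200/270 = 51.9 | exp(0.389) = 1.48 | exp(0.550) = 1.73 |
| 100/300 | 100 × 200/300 = 66.7 | exp(0.343) = 1.41 | exp(0.485) = 1.62 |

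Even on the less favourable liability scale, the joint test for a medium effect has about 88–95% power at 270–300 infants.

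**The case against.** The strongest reply is that f² can be applied to a 0/1 response and that nothing in the design turns on these figures. Both parts stand. A reader might infer that the yes/no outcome alone makes the figures invalid and costs a further 12–47 points. It does not: step 2 recovers Cohen's values at every case fraction when f² refers to case status. The loss appears only on a liability scale that the protocol never invokes.

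Other stronger readings also lack support:

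- *About 17 cases for ten predictors, or a type I error near 12%, at n = 50.* This assumes that n counts infants with one record each, that one third are cases, and that an uncorrected logistic likelihood-ratio test is used. The protocol gives no unit for the 50 and names no such test.
- *The ten predictors mix clinical and microbiome terms.* They are not listed. What can be said is that a joint test of all ten is not the adjusted microbiome effect.
- *The protocol claims 50 infants suffice.* Its own 47% for a medium effect says otherwise, and the section also gives about 200 samples for community profiles and more than 100 for some structural equation models.

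GLM may mean generalized linear model, and the link function can be left to the analysis plan; its absence is no finding. The Aims also plan mixed models of microbiota against metabolome, where f² on a continuous response could fit. But the paragraph ties these figures to disease risk. None of this makes 82%, 47% or 74% reproduce, or turns a joint test at n = 50 or 100 into the planned analysis.

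**Conclusion.** The point holds as a misstatement of power. From the printed inputs, the overstatement is about 9 points (82 against 73), 14 points (47 against 33) and 3 points (74 against 71); the 99% is right for the test it describes. That part needs no assumption beyond Cohen's formula. Independently of the arithmetic, the four figures answer a different question, at sizes other than the planned 270–300 infants. Any larger shortfall depends on the unstated effect scale and should be presented as conditional.

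A reader might go on to infer that the study is underpowered for its disease model. The figures do not support that: under the assumptions in step 3, the planned numbers look adequate for moderate effects. Repeated records are not modelled in these checks, so the odds ratios are a guide.

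**What to change.** Replace the four figures with power, or a detectable odds ratio per SD of one microbiome covariate after adjustment, at 70–100 cases and up to 200 non-diseased infants. The values in step 3 can serve as a first version, with the one-record assumption stated or replaced by an assumed within-infant correlation. State the scale on which the effect is expressed. Do not present n = 50 as giving 82% power. If the Cohen figures are kept as a rough guide, print 73%, 33%, 99% and 71%, correct R² to 0.26 and 0.13, and label them as a joint test of ten predictors.

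The cost is one rewritten paragraph, a short recalculation, and less favourable stated figures at n = 50 and n = 100. No infants, samples or analyses are added.

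### The GLM power statement prints multiple R as R² and overstates three of its four powers, most of all at n = 50

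*Protocol article*

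**What the plan says.** The last item under Sample Size Estimates in the protocol article supports the mixed-effects models of disease risk with a power calculation by Cohen's method: "we calculate that a GLM would have a power of 82% with 10 predictors and 50 for a" large effect, at the 5% level. The parenthesis and the next figure read "0.51) at the 5% level of significance, and a power of 47% for a" medium effect, which is labelled f² = 0.15 and R² = 0.36. At n = 100, "the calculated powers are 99% for a large effect size and 74% for a medium effect size". The text does not say whether 50 and 100 are infants or samples. It then adds, without a condition: "Including random effects in the GLM would increase power at the same effect size", on the ground that the random effect absorbs part of the residual variance. The section on direct and indirect impact of risk factors describes repeated-measures models with the case as the random effect.

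**The concern.** Each parenthesis gives two versions of one effect size, f² and R², and the two do not agree. Every input to the power figures is printed, so the figures can be checked, and most do not come out. The errors all run in the plan's favour.

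Two misreadings follow. A reader who takes R² at its printed value will think that a medium effect explains 36% of the variance when f² = 0.15 implies 13%, and that a large one explains 51% rather than 26%. A reader who takes the powers at face value will think that 50 units are enough for a large effect.

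The random-effects sentence adds to this. It suggests that the printed powers are conservative for the models actually planned, which need not be so for every predictor.

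**Working it through.** **Inputs**, all from Sample Size Estimates: 10 predictors (u = 10); n = 50 and n = 100; α = 0.05; f² = 0.35 (large) and 0.15 (medium).

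**Step 1: the R² labels.** R² = f²/(1 + f²).

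- Large: 0.35/1.35 = 0.259; the square root is 0.509.
- Medium: 0.15/1.15 = 0.130; the square root is 0.361.

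The printed 0.51 and 0.36 equal the square roots to two decimals, so they are R. Taken literally as R², they would mean f² = 0.51/0.49 = 1.04 and 0.36/0.64 = 0.56. Power at n = 50 would then be 99.9% and 93%, so the printed powers do not belong to that reading either.

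**Step 2: the powers.** Cohen's test that all 10 coefficients are zero uses a noncentral F with u = 10, v = n − 11 and noncentrality λ = f²·n. Power is the probability of exceeding the central F critical value.

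| n | f² | v | λ | F critical | Power | Stated |
|---|---|---|---|---|---|---|
| 50 | 0.35 | 39 | 17.5 | 2.08 | 72.6% | 82% |
| 50 | 0.15 | 39 | 7.5 | 2.08 | 32.6% | 47% |
| 100 | 0.35 | 89 | 35.0 | 1.94 | 98.8% | 99% |
| 100 | 0.15 | 89 | 15.0 | 1.94 | 70.7% | 74% |

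Only the 99% is reproduced. The differences are 9.4, 14.4 and 3.3 points.

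**Step 3: could another convention explain the stated figures?** Powers are listed as n = 50 large/medium, then n = 100 large/medium. The stated set is 82/47, 99/74.

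- v wrongly set to n: 84.6/41.9, 99.5/76.8.
- Large-sample chi-square: 83.5/40.7, 99.4/76.0. This is within 2 points on three figures but misses the 47%.
- α = 0.10: 83.3/46.2, 99.6/81.2. This contradicts the stated 5% and misses the 74%.

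A grid over the degrees of freedom and the noncentrality, with 10 predictors at 5%, still missed at least one figure by 3.9 points. No single setting tried matched all four within 2 points.

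**Step 4: n for 80% power.**

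- Large: n = 56 gives 79.8% and n = 57 gives 80.8%.
- Medium: n = 117 gives 79.7% and n = 118 gives 80.1%.

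**Step 5: the random-effects sentence.** For a predictor that is constant within an infant, with the total number of samples fixed, the effective n is the number of samples divided by 1 + (m − 1)·ICC, where m is samples per infant. The documents give no ICC and no m for this model, so the following values are assumptions. They take 100 samples and f² = 0.35, for which independence would give 98.8%.

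| m | ICC | Design effect | Effective n | Power |
|---|---|---|---|---|
| 2 | 0.2 | 1.2 | 83.3 | 96% |
| 2 | 0.5 | 1.5 | 66.7 | 89% |
| 5 | 0.2 | 1.8 | 55.6 | 79% |
| 5 | 0.5 | 3.0 | 33.3 | 44% |

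This shows only that the sentence is not true in general. It does not estimate the power of this study.

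**The case against.** The strongest reply is that little depends on these figures. A reader might infer that they set the size of the disease-risk modelling and that the study is therefore too small. The documents do not support that. Sample Size Estimates rests the sizes on published data and practical constraints, and links the 480 recruits to ELFIN's timetable and to expected event rates that yield 70 to 100 diseased infants. The case definitions section adds up to 200 non-diseased infants. If those 270 to 300 infants are independent units, the same formula gives more than 99% power for both effect sizes. Nowhere is n = 50 named as the sample for the disease model, and the interim criterion does not use these powers. This reply stands, and it limits the severity.

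It is also true that the medium-effect figures were already printed below 80%, so correcting them changes no conclusion.

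On random effects, a reader might take the protocol to claim that they can only raise power, or might conclude that the sentence is simply false. Neither is right. The text does not say only, and the statement can hold for predictors that vary within an infant, such as the repeatedly sampled microbiome. The fault is the missing condition.

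Nor do the documents establish that n counts samples. The unit is not given here, and the same section counts infants for the VOC calculation and samples for the microbiome calculation.

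None of this rescues the printed R² values or the three powers.

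**Conclusion.** The point holds as an error in stated figures and should be fixed. The R² mislabel is certain, since it follows from the definition alone. The power overstatement rests on the standard reading of the method that the article names: the overall F test of 10 predictors, with n independent units. Under that reading the large effect at n = 50 falls short of 80% by 7 units (57 − 50). It is the only one of the four figures whose standing against 80% changes. The recruitment target and the planned analyses are not affected. The random-effects sentence needs a qualifier; how much clustering would matter here cannot be computed from the documents.

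**What to change.** Restate the calculation as the power of the overall test of 10 predictors at the 5% level: f² = 0.35 (R² = 0.26) gives 73% at n = 50 and 99% at n = 100; f² = 0.15 (R² = 0.13) gives 33% and 71%; 80% power needs n = 57 and n = 118. If another method produced the stated figures, name it with its settings.

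State whether n counts infants or samples.

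Keep the random-effects sentence but qualify it: the gain can apply to predictors that vary within an infant, whereas for infant-level predictors such as trial arm or gestation, repeated samples from one infant add less information than the same number of independent infants.

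The cost is wording only. The stated figures become less favourable, and no design element has to change.

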
### Statistical Analysis

There are three major modeling issues that have to be addressed in this analytical pathway:
(i)the multivariate nature of the microbiome and metabolome, and data generated from immunohistochemistry;(ii)the longitudinal/developmental component in the neonate, which will lead to repeated measures of disease state and microbiome on the same individuals, and(iii)the interdependence and interactions between different predictors, which may have both direct and indirect effects on incidence and progression of disease.

The analytical approach used in this study will focus on modeling the relationship between putative risk factors, trial interventions, and incidence of NEC and LOS from longitudinal data capturing variation in both risk factors and disease through time, and the any differences in non-diseased cases between trial arms. We will use a progressive modeling strategy based on combining multivariate analyses of micro- and metabolomic immunological data, with mixed-effect modeling of outcome in relation to drivers of disease; and finally, mixed-effect SEM to quantify the importance of interacting factors and drivers. Specifically, we will
(i)quantify the impacts of individual risk factors in causing disease;(ii)quantify the effects of direct and indirect risk factors on disease;(iii)quantify the dynamics of pathogens, the neonatal microbiome, the immune response, and their impact on outcomes, and(iv)identify the impacts of trial interventions and clinical management on the drivers and disease.

